#### Economic Evaluation

The economic evaluation will be performed from a societal and a public health care perspective. Two multilevel models (MLMs) will be specified, one for costs and one for effects, which consider the hierarchical structure of the data. For effects, normal-based 95% CIs will be estimated. For costs, 95% CIs will be estimated using bias-corrected and accelerated (BCa) bootstrapping with 5,000 replications (102). MLMs will be combined with cluster bootstrapping, which is recommended for resampling clustered data (103). Across the three treatment groups, the adjusted mean costs and QALYs will be compared to assess if any of the treatments are less effective and more expensive than the other treatments. If so, incremental cost-effectiveness ratios (ICERs) will not be estimated in relation to that treatment (104). Otherwise, ICERs will be estimated by calculating the difference in costs between two treatment options divided by the difference in effectiveness of these two treatment options. The joint uncertainty surrounding costs and effects will be summarized using cost-effectiveness acceptability curves [CEACs; (105)]. CEACs show the probability of an intervention being cost effective in comparison with the alternatives for a range of different ceiling ratios.

#### Moderator Analyses

Predictors and moderators of treatment outcome will be analyzed on an exploratory basis with a priori defined potential moderators. We will conduct univariate exploratory analyses by entering the respective baseline variable as a three-way interaction term in the three-level random slope model. Moreover, we will also investigate interindividual differences in treatment effects by utilizing the EffectLiteR approach (106), that allows to include interactions between the treatment variable and a range of categorical and continuous (latent) covariates, because it uses a multigroup structural equation model for the estimation of parameters.

#### Mobile Sensing

The analysis of the mobile sensing data will be divided into two parts. Firstly, correlation analyses will be conducted to investigate associations between digital features (e.g., smartphone usage time) and mental health outcomes. Correlation coefficient r will be used for the analysis, which ranges between 0 (no relationship) to 1 (perfect relationship; −1 perfect negative relationship). For all correlation analyses, the alpha-level will be 5%. *P*-values will be adjusted for multiple testing using the procedure proposed by Holm (107, 108). Full information maximum likelihood will be applied to deal with missing values in the correlation analysis (108, 109). Secondly, we will build different prediction models to predict mental health. Both “traditional” multilevel models relying on significance tests and machine learning will be used. Building and modifying machine learning models is a highly iterative process with many changing factors to find the optimal model (e.g., architecture, optimizer, included features). Hence, defining a-priori model is impossible. However, a range of approaches will be tested, this includes: Random Forest models, Support Vector Machine (SVM), XGBoost (XGB), K-Nearest Neighbor (KNN), and Logistic Regression [LR; (110–114)].

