## Methods

### Study Design

A three-armed multicenter large-scale pragmatic, cluster-randomized controlled trial (cRCT) will be conducted comparing the clinical and cost-effectiveness of two implementations of blended therapy (PSYCHOnlineTHERAPY_fix/flex_) compared to standard CBT (CBT_standard_). Quantitative trial outcomes will be complemented by qualitative interview data on the acceptance, feasibility, and optimization potential of PSYCHOnlineTHERAPY in order to gain in-depth insights in participants' experiences. A smart-sensing sub-study, examining ecological day-to-day digital behavior variables via passive smartphone sensing, aims to provide psychotherapy process insights (33).

This clinical trial has been approved by the ethics committee of the German Psychological Society (DGPs no. [name]) and will be reported in accordance with the Consolidated Standards of Reporting Trials (CONSORT) Statement 2010 and the extensions for reporting pragmatic trials, non-inferiority trials, cluster randomized trials, multi-arm parallel group trials, and trials on psychological interventions (34–39). Qualitative data analyses will be reported following the Consolidated Criteria for Reporting Qualitative Studies (COREQ) checklist (40). Cost-effectiveness analyses will be reported according to Consolidated Health Economic Evaluation Reporting Standards statement [CHEERS; (41)] and the guidelines from the International Society for Pharmacoeconomics and Outcomes Research [ISPOR; (42)]. This trial protocol was created according to SPIRIT guidelines (43). The study has been registered in the German clinical trial register under DRKS00023973.

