#### Mobile Sensing

Mobile sensing data will be collected via the “AWARE” framework [https://awareframework.com; (84)]. In short, the AWARE app allows the collection of data on smartphone usage (e.g., usage time and frequency, GPS data, communication behavior) as well as ecological momentary assessments in form of questionnaires. For technical details on how the data is collected as well as an in-depth description of privacy and data security of the app and the server please see the concept paper of the AWARE framework (84).

After giving consent to participate in the main trial patients are informed about the optional mobile sensing sub-study and asked whether they would like to participate. Participants that provided their additional informed consent are instructed to install the mobile application AWARE on their personal smartphones. After installation participants can choose which of the following data points are collected over the 6 months:

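### The mobile-sensing correlation step names only r, with no unit of analysis and no handling of repeated measures, although the data repeat within patients over six months

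*Protocol article*

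**What the plan says.** The Study Design section gives the sub-study a day-to-day purpose: "examining ecological day-to-day digital behavior variables via passive smartphone sensing, aims to provide psychotherapy process insights". The Mobile Sensing section under Assessments says that, once the app is installed, patients choose "which of the following data points are collected over the 6 months". It lists passive phone data and repeated short questionnaires, including a four-item depression and anxiety measure. Taking part is optional.

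The Mobile Sensing section under Statistical Analyses splits the analysis into two parts.

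- **Associations.** "Firstly, correlation analyses will be conducted to investigate associations between digital features (e.g., smartphone usage time) and mental health outcomes". On the statistic: "Correlation coefficient r will be used for the analysis, which ranges between 0 (no relationship) to 1". On the level: "For all correlation analyses, the alpha-level will be 5" per cent. On multiplicity, the p-"values will be adjusted for multiple testing using the procedure proposed by Holm". On incomplete data: "Full information maximum likelihood will be applied to deal with missing values in the correlation analysis".
- **Prediction.** Here, and only here, "multilevel models relying on significance tests and machine learning will be used".

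For the association part the article does not say whether r is taken over patients or over patient-occasions. It names no repeated-measures, within-person or multilevel form of r.

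**The concern.** Several records from one patient are not independent, and the usual test of r assumes that they are. The article has gone as far as fixing the statistic, the level, the multiplicity procedure and the missing-data method for this step. It has left out the one element that decides whether the test is valid and what it estimates.

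Two things are at stake. On patient-occasion records, the long list of passive features could yield Holm-adjusted findings that come from counting the same patients many times. On patient summaries, the question changes. Whether patients who use their phone more are more depressed is not the same as whether a patient is more depressed on days of heavier use. The two associations can differ in size and in sign, and only the second speaks to the day-to-day process aim.

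The article accounts for nesting elsewhere. It plans a three-level model for the primary outcome, and multilevel models with cluster bootstrapping for the economic evaluation.

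**Working it through.** **Inputs.** From the article: r, a 5% level, Holm, six months of sensing. The 5% is a chosen level, so there is no derived figure to reproduce. The article gives no sub-study sample size, sampling frequency or within-patient correlation. The following are therefore assumptions:

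- records per patient, m: 6 or 26 (26 is about weekly over six months);
- within-patient correlation, ICC: 0.3, 0.5 or 0.7, equal in both variables and exchangeable over time;
- sub-study size: 100 or 300 patients;
- two-sided test (the article does not state the side).

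**Reading 1: r on patient-occasion records.** With no true association, the variance of pooled r is inflated by 1 + (m − 1) × ICC². The true level of a nominal 5% test is 2 × [1 − Φ(1.96 / √inflation)].

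| m | ICC | Inflation | True type I error |
|---|---|---|---|
| 6 | 0.3 | 1 + 5 × 0.09 = 1.45 | 0.10 |
| 6 | 0.5 | 1 + 5 × 0.25 = 2.25 | 0.19 |
| 6 | 0.7 | 1 + 5 × 0.49 = 3.45 | 0.29 |
| 26 | 0.3 | 1 + 25 × 0.09 = 3.25 | 0.28 |
| 26 | 0.5 | 1 + 25 × 0.25 = 7.25 | 0.47 |
| 26 | 0.7 | 1 + 25 × 0.49 = 13.25 | 0.59 |

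Simulation with 1,000 data sets per setting agrees: 0.10 to 0.30 for m = 6 and 0.28 to 0.60 for m = 26. The result hardly depends on whether there are 100 or 300 patients.

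**Does Holm help?** Holm corrects for the number of tests and takes each p-value as valid. With 10 null features, 100 patients, m = 26 and ICC 0.5, the simulated familywise error after Holm was about 0.96, against a nominal 0.05 (400 data sets). With patient means in the same data it was about 0.07. Full information maximum likelihood deals with missing values and does not make records independent.

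**Reading 2: r on one summary per patient.** In the same simulations the nominal 5% test on patient means rejected in 4.0% to 6.1% of null data sets. That is 5% within simulation error.

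**What each reading estimates.** Suppose, for illustration, a between-person correlation of 0.5, a within-person correlation of −0.3 and ICC 0.5 in both variables.

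- Pooled records: r ≈ 0.5 × 0.5 + 0.5 × (−0.3) = 0.10 (simulated mean 0.09). This describes neither level.
- Patient means, m = 26: r ≈ [0.5 × 0.5 + 0.5 × (−0.3)/26] / [0.5 + 0.5/26] = 0.244/0.519 = 0.47. This is close to the between-person value and shows nothing of the −0.3.

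**Separating the levels.** A correlation of deviations from patient means, with N(m − 1) − 1 degrees of freedom, rejected in 4.2% to 6.8% of null data sets. Both levels can therefore be tested at about the stated 5% under these assumptions.

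**The case against.** The strongest reply is that the article never says records are pooled. A reader might infer from r at 5% that pooled p-values are planned and will be far too small. The text does not support that. The trial's main symptom measures give one value per patient per assessment. Correlating an aggregated feature with such a value needs one row per patient and keeps the 5% level. This part stands, so the inflation is conditional on the record-level reading.

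Second, the unit of analysis in an optional sub-study is the kind of detail an analysis plan may settle. This stands in part. The plan is not shown and may name the unit. However, the article does fix the statistic, and plain r has a defect on either reading: invalid p-values on records, or no view of within-person change on patient summaries. Only a within-person or repeated-measures form would avoid both, and none is named.

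Third, the same section already plans multilevel models, so the authors know the data are nested. That is true, but those models belong to the prediction part and do not cover the Holm-adjusted correlation tests. It is also fair that no sentence requires the association step to meet the process aim alone.

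Fourth, every input to the illustration is assumed. That is correct, and it is why a range is given.

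**Conclusion.** The point holds as a conditional one. The association step fixes r, 5%, Holm and full information maximum likelihood, but gives neither a unit of analysis nor any handling of repeated measures.

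- On patient-occasion records, the true type I error at nominal 5% would be about 10% to 59%. This assumes 6 to 26 records per patient and an exchangeable ICC of 0.3 to 0.7 in both variables.
- On one summary per patient there is no such inflation, but only a between-person association is estimated, and the day-to-day aim is left to the other analyses.

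The documents do not show which reading is meant, so it would be wrong to conclude that the planned p-values are invalid. The sub-study is optional and does not bear on the primary non-inferiority conclusion. This is a cheap improvement, not a threat to the trial.

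**What to change.** State the unit of analysis for the association step and replace plain r by a two-level model per feature, with occasions within patients and a patient random effect. Enter the patient's mean of the feature (between) and the deviation from that mean (within) as separate terms. Report both as standardised coefficients, and apply Holm to both sets of p-values. The assumption about correlation between neighbouring days should be stated as well, since a random intercept alone treats all days of a patient as equally correlated.

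The cost is a few sentences in the analysis plan, and the multilevel tools are already foreseen in the same section. The downside is two coefficients per feature. The Holm family doubles, from k to 2k tests for k features, with some loss of power per test.

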#### Qualitative Data Analysis

All qualitative data will be audiotaped and transcribed verbatim using the software MAXQDA. The analysis of qualitative data will be based on qualitative content analysis. An inductive-deductive approach will be applied linked to the theory-based interview guide. To establish reliability of results (indicated by intercoder agreement), two independent raters will code all transcripts on the basis of coding guide and rules. The development of this coding guide follows an iterative process with consensus finding. A follow-up survey with the interviewed samples enable the validation of emergent themes. A higher representativity of the results should enable the subsequent validation of the identified themes by a survey with all participants. Meaningful differences in the identified themes between the two groups PSYCHOnlineTHERAPY_fix_ and _−flex_ will be described through the report of group differences of at least 25%.

## Discussion

PSYCHOnlineTHERAPY will be one of the largest ever-conducted psychotherapy trials with 900 patients from 75 psychotherapy standard outpatient care practices. At the same time PSYCHOnlineTHERAPY has the potential of innovating psychotherapy in the near future by extending the ways of conducting psychotherapy on-site, video-conference based, Internet-and mobile-based, or blended using potentially all of these possibilities as examined in PSYCHOnlineTHERAPY. The rigorous health care services approach of PSYCHOnlineTHERAPY, embedded into standard care with even new billing codes as part of the underlying PNP contract for the new psychotherapeutic service of the Internet- and mobile-based intervention modules will ensure the timely implementation of blended therapy into standard care, in case of PSYCHOnlineTHERAPY being effective and cost-effective. Moreover, the elaborated evaluation concept on moderators and mediators including a smart sensing sub-study, will provide deeper insights into the black box psychotherapy, i.e., the active components and the mechanisms of change (32, 115) as well as the differential indication question on which type of psychotherapy and specific technique works for whom at what time in the treatment course (9, 116–118).

### Potential Problems and Solutions

In order to avoid selection bias, PSYCHOnlineTHERAPY follows strict trial role division with Ulm University as principle investigator, intervention content and IT-solution provider and interface to health care service providers and stakeholders. Evaluation of PSYCHOnlineTHERAPY takes place at University of Erlangen-Nuernberg. Thereby, the University of Erlangen-Nuernberg has established a work flow ensuring that randomization, administration of participants, and outcome assessments (interviews) will be conducted independent of each other. Particularly outcome assessors are kept blind toward trial arm allocation. At the beginning of each telephone interview, patients are asked to keep their trial arm allocation disclosed.

Trial arm contamination might occur in joint practices. Hence, psychotherapists in joint practices are randomized and allocated jointly in the same trial arm condition. Resulting clustering effects will be compensated statistically. Different to cRCTs in general practices patient-level trial arm contamination is rather unlikely, as patients do not switch psychotherapists in due course or during times of absence (e.g., vacation) of their psychotherapists. Patients will be asked whether they already took part in PSYCHOnlineTHERAPY before.

Considering that therapeutic alliance, which depends also on the characteristics of the psychotherapists, is one of the most important variables predicting the outcome of psychotherapy (119, 120), randomizing therapists runs the risk of clinically important baseline imbalance. Cluster size was optimized for the pre-specified non-inferiority margin, however, between trial arm baseline imbalance regarding therapist competency needs to be considered carefully when interpreting the final trial results.

Study and intervention protocol adherence will be improved by structured training courses, regular contacts with study psychotherapists as well as assessed via therapists' documentation of their psychotherapies.

## Conclusion

The present cRCT PSYCHOnlineTHERAPY aims to examine the non-inferiority and cost-effectiveness of two blended therapy versions embedded in standard care. As one of the largest psychotherapy trials ever conducted, PSYCHOnlineTHERAPY has the potential to innovate the way of how psychotherapy is provided, thereby exploring its mechanisms of change at the same time.

## Trial Status

Patient Recruitment start is scheduled for January 2021.

## Dissemination

Trial results will be presented on national and international conferences and published in peer-reviewed journals. Access to the final trial dataset can be provided on request depending on to be specified data security and data exchange regulation agreements.

## Ethics Statement

The studies involving human participants were reviewed and approved by Ethics Committee of the German Asssociation of Psychology. The patients/participants provided their written informed consent to participate in this study.

## Abbreviations

APOI: Attitudes toward Psychological Online Interventions Questionnaire
AUC: area under the curve
AQoL-8D: Assessment of Quality of Life
BCa: bias-corrected and accelerated
CBT: cognitive behavioral therapy
CBTSQ: Cognitive-Behavioral Skills Questionnaire
CEAC: cost-effectiveness acceptability curve
CEQ: Credibility/Expectancy Questionnaire
CI: confidence interval
cRCT: Cluster-randomized controlled trial
CSQ: Client Satisfaction Questionnaire
CTS: Childhood Trauma Screener
CONSORT: Consolidated Standards of Reporting Trials
COREQ: Consolidated Criteria for Reporting Qualitative Studies
DSMB: Data Safety Monitoring Board
EBPAS-D36: German version of the Evidence-based Practice Attitude Scale-36
FRAPT: “Fragebogen zur Messung persönlicher Therapieziele”
F-SozU K-6: Brief form of the Perceived Social Support Questionnaire
GAD-7: Generalized Anxiety Disorder Screener
HAM-A: Hamilton Anxiety Rating Scale
ICC: Intra-Cluster Correlation Coefficient
ICER: Incremental cost-effectiveness ratio
ITT: Intention-to-treat
IMI: Internet- and mobile-based intervention
KNN: K-Nearest Neighbor
LPFS-BF 2.0: Level of Personality Functioning Scale—Brief Form 2.0
LR: Logistic Regression
MARS-G: German version of the Mobile Application Rating Scale
MDR: Medical Device Regulation
MHSES: Mental Health Self Efficacy Scale
MLM: multilevel model
NEQ: Negative Effects Questionnaire
NoMAD: Normalization Measure Development Questionnaire
PIC/S: Pharmaceutical Inspection Cooperation Scheme
PHQ-4/-9: Patient Health Questionnaire
PHQ-ADS: Patient Health Questionnaire Anxiety and Depression Scale
PNP: Psychotherapy, Neurology, Psychosomatic and Psychiatry (selective health care services contract)
PP: Per-protocol
QALY: Quality adjusted life year
QIDS-C: Quick Inventory of Depressive Symptomatology in its clinician-rated version
(S)AE: (serious) adverse event
SCID-5: Structured Clinical Interview for DSM-5 Axis I Disorders
SMST: Self-Management Self-Test
SVM: Support Vector Machine
TAI: Therapeutic Agency Inventory
TAU: Treatment as usual
TiC-P: Trimbos Institute and Institute of Medical Technology Questionnaire for Costs Associated with Psychiatric Illness
TDF: theoretical domains framework
UCLA: UCLA Three-Item Loneliness Scale
UTAUT: Unified Theory of Acceptance and Use of Technology
WAI-SR: Working Alliance Inventory - Short Revised
XGB: XGBoost
ZUF-8: German Version of the CSQ.
